### Blinding

Given the nature of the interventions, local researchers cannot be blinded as to the treatment delivered. Central research staff will be unaware of treatment condition when carrying out analyses to assess outcomes.

### Experimental intervention (MDFT)

MDFT is delivered by individual therapists who are part of teams of 3 - 5 CTRADA certified therapists, with one of them additionally serving as team supervisor.

MDFT is carried out according to the MDFT treatment manual http://kap.samhsa.gov/products/manuals/cyt. MDFT lasts 5 to 7 months, depending on the severity of the case. On average, sessions are scheduled twice a week - in roughly equal proportion to be held with the adolescent, parent and family (adolescent + parent) respectively, and additionally with representatives of other systems (school, work, friends, agencies) present. Sessions can take place at the office, but also at the family's home or any other convenient location. Scheduling sessions is not limited to regular office hours. Each team meets once a week to discuss cases and issues.

### Control condition

INCANT compares MDFT with treatment as usual (TAU). TAU is carried out by the same treatment centres offering MDFT, but procedurally separated to avoid 'contamination' of therapists and participants between the experimental and control conditions.

TAU varies between the participating countries, but has in common motivational interviewing and elements of cognitive-behavioural therapy (CBT) in addition to more general individually-based substance abuse counselling. TAU in Belgium, Germany and Switzerland is characterized by a mixture of CBT and individual drug counselling, and in the Netherlands by a cognitive-behavioural approach tailored to adolescents (Leefstijltraining). The Dutch TAU therapists have received formal training in TAU for the purpose of the trial. In France, MDFT is compared with TAU (a mix of CBT and individual counselling methods as used in daily practice) and TAU-e (TAU-explicit = idem, but then manualized). The French TAU-e therapists have been trained in using the TAU-e manual; the TAU therapists have not received special training for INCANT. Below, French TAU and TAU-e are jointly referred to as 'TAU'.

Across sites, we set minimal requirements for TAU. The control treatment matches MDFT in total duration of the therapy. MDFT and TAU do not differ in assessments and in general procedures such as therapists working in a team; applying substance use urine tests; communication with referral sources and authorities; and occasional referral to additional treatments to deal with psychiatric co-morbidity and medication. Furthermore, MDFT and TAU do not differ in session duration; drug education; and the way the adolescent is individually trained in substance use relapse prevention, with emphasis put on coping with stress, managing anger, increasing assertiveness in interpersonal contacts, and addressing (negative) thoughts about substance use.

TAU sessions are individual (with the adolescent). Parents may be seen alone or in groups, purely for reasons of drug education and mutual support, but any element of systems therapy involving the parent and other systems into the treatment is excluded.

### Monitoring of treatment integrity

In all INCANT conditions, the therapists are required to submit *treatment contact logs *or data from the centre's treatment register providing the same insight: number, duration, spacing and composition of sessions (therapist meeting whom). These data are used throughout the study to ensure that all therapists meet the pre-set minimum level of treatment intensity. In MDFT, these logs are monitored by CTRADA (University of Miami) staff to ensure fidelity to MDFT parameters of contact with adolescent, parent, family, and external systems sessions.

Based on treatment adherence evaluation guidelines [5], 25% of MDFT cases are selected for transcribing one family session, which is translated in English to allow CTRADA to rate these sessions for MDFT treatment adherence with a validated 7-point Likert scale targeting 16 therapists' interventions crucial to MDFT [9].

### Therapists

All MDFT (n = 25) and TAU therapists (n = 29) are experienced in treating adolescents with multiple problem behaviour. MDFT therapists are similar to TAU therapists with regard to age (MDFT vs. TAU across sites: 42 vs. 40 years of age) and gender (48% male in MDFT, and 35% in TAU).

CTRADA trained the sites' MDFT teams in 2004 - 2005, with plenary training weeks in Europe and Miami; evaluation of MDFT family sessions and session logs; bimonthly telephone consultation calls; and site visits by CTRADA staff. Booster training was given in 2006 and 2007. TAU training in the Netherlands and TAU-e training in France were delivered locally by senior clinical staff from the treatment centre (France) or by a CBT training unit (the Netherlands).

### Remuneration

The adolescents but not the parents are remunerated in local currency, either by voucher or in cash, for completing follow-up assessments, for a total of € 60 - 70 accumulated across all follow-up assessments. No remuneration is given in Belgium and France, where this would run counter to legal requirements.

### Assessments

Assessments take place at baseline and at 3, 6, 9 and 12 months post-randomization, at the treatment centre, the home of the family or any other convenient place. Additional information is gathered by phone or mail. Questionnaires are self-administered by the adolescent or parent, or if required completed by a researcher, who has been trained by INCANT project staff and is working under the guidance of three Instruction Manuals (for baseline, 3-months FU, and later FU, respectively; http://incant.eu). Table 1 shows the questionnaires and interviews delivered.

**Table 1 T1:** Measures used in INCANT at baseline and at four post-randomization follow-up points

Surveys	Baseline	Month 3	Month 6	Month 9	Month 12
	**Adolescent**				

Cannabis section, ADI-Light	•				•
Alcohol section, ADI-Light	•				•
Other drugs, ADI-Light	•				•
Urine analyses of substance use	•	•	•	•	•
TLFB	•	•	•	•	•
Adolescent Interview	•		•		•
Life Events	•				•
PEI	•		•	•	•
Cannabis section, ADI-Light	•				•
Alcohol section, ADI-Light	•				•
Other drugs, ADI-Light	•				•
FES	•		•	•	•
YSR	•		•		•
Treatment satisfaction, adolescent			•		

	**Parent**				

Parent Interview	•		•		•
CBCL	•		•		•
Treatment satisfaction, parent			•		

Abbreviations: ADI = Adolescent Diagnostic Interview, CBCL = Child Behavior Check List, FES = Family Environment Scale, PEI = Personal Experience Inventory, YSR = Youth Self-Report.

### Study hypotheses

INCANT addresses a number of research questions:

#### Primary outcomes

Does MDFT exceed TAU in reducing the use of cannabis and the prevalence of (symptoms of) cannabis disorders? We assume that adolescents assigned to MDFT will decrease their use of cannabis more than adolescents in TAU between baseline and 6-months follow-up assessments. This treatment gain is expected to be maintained better in MDFT than in TAU in the period between 6- and 12-months follow-up.

Moreover, youth assigned to MDFT will be less likely to meet diagnostic criteria of cannabis disorders between baseline and the 12-months follow-up assessment than TAU youth.

#### Secondary outcomes

An important secondary outcome is the extent in which the treatments succeed in engaging and retaining cases into the respective intervention programme. We assume that MDFT will do better than TAU in this respect.

Further, we hypothesize that MDFT exceeds TAU in attenuating established risk factors for persistence of cannabis disorders: other substance use, internalizing and externalizing mental disorder symptoms, family dysfunction, school problems, delinquency. For each of the factors mentioned, a hypothesis has been formulated and measures have been selected.

Finally, we examine the degree in which MDFT and TAU are appreciated by adolescents and parents, assuming that MDFT will receive higher satisfaction ratings than TAU.

### Measures

Table 1 gives an overview of the instruments - questionnaires and structured interviews - to be applied at baseline and four follow-up assessment points, distinguishing measures administered to youth and parent.

#### Background and demographic information

The *Parent and Adolescent Interviews *[9] have been tailored to gather demographic data on gender, age and ethnicity, and on family composition, history of familial drug use and mental health problems, adolescent substance use history and court involvement, treatment history and service utilization, school functioning, peer relationships, and pastime activities.

#### Primary outcomes: cannabis use

Cannabis use and other substance use disorders are assessed with the *Adolescent Diagnostic Interview-Light *(ADI-Light; [10]). This brief structured, multi-axial interview is based on DSM-IV criteria for substance use disorders in adolescents. At baseline, an ADI-Light established diagnosis of recent cannabis use disorder was required to enrol the case into INCANT.

We measure the frequency of adolescents' cannabis use with the *Timeline Follow-Back *method (TLFB; [11] as adapted and validated for adolescents [12]. The TLFB obtains retrospective reports of daily cannabis use for the 90-day period prior to each assessment, using a calendar and other memory prompts to stimulate recall.

Adolescents' preoccupation with and motivation for substance use are recorded with the Personal Involvement with Chemicals Scale from the *Personal Experiences Inventory *(PEI). The psychometric properties of this scale are excellent. A reliability score of α = 0.97 has been reported [13].

#### Secondary outcomes: adolescents' psychosocial functioning

We assess adolescents' internalizing, externalizing, and psychotic symptoms with the *Youth Self Report *(YSR). This instrument is reliable and valid across a variety of studies, populations, and languages (including Dutch, German and French) [14,15]. We also apply the 'parent version' of the YSR, which is called CBCL (*Child Behavior Checklist*). Like the YSR, the CBCL has excellent (test-retest, internal consistency, inter-rater) reliability and (construct, concurrent, discriminant) validity in various languages [e.g., [14,16]].

#### Secondary outcomes: family functioning

Family conflict and cohesion are measured with the respective sub-scales from the *Family Environment Scale *(FES), a widely used and well validated self-report measure [17], completed by the teen. The FES has adequate psychometric properties. The Conflict and Cohesion parts have good reliability (α = 0.75 and α = 0.78, respectively) [17,18].

#### Secondary outcomes: treatment satisfaction

At 6-months follow-up, corresponding to the end of a full course of treatment, adolescents and parents each complete the *Satisfaction Scale*, which measures satisfaction with treatment received along four dimensions: (1) access to and convenience of treatment arrangements, (2) adolescent's treatment process and relationship with the therapist, (3) parent and family services, and (4) global satisfaction. These scales have adequate reliability and validity [19].

### Analyses

The analyses will be based on the intent-to-treat principle, such that all cases will be assessed at all time points regardless of therapy and therapy dosage received.

We will pool the data from all subjects from all sites for analyses with country/site as a covariate. If differences between sites are statistically significant, within-site analyses will be done for the topics concerned.

Most measures in the trial are repeated (Table 1). For repeated measures we will apply both a mixed model for repeated measurements and Latent Growth Curve Modelling (LGM). LGM serves to model individual differences in change as measured by instruments such as the TLFB and PEI. LGM has the advantage of charting individual change trajectories [7] while producing unbiased estimates when data are missing [20]. Change trajectories will be evaluated across all assessment points.

The LGM models are statistically equivalent to random coefficient regression models.

As for MDFT treatment adherence, we will use equivalence testing procedures to compare the mean MDFT adherence scores to benchmark values for therapists trained in U.S.-based trials of MDFT, to see if they are statistically equivalent. We will use an a priori equivalence interval of +/- 20 percent. A 90% confidence interval will be calculated around the mean difference between the adherence scores in INCANT and the benchmark values. If the values for the 90% confidence interval fall within the a priori equivalence interval, the scores are considered to be statistically equivalent [21].

To meet the challenges of data analyses, a statistical workgroup has been formed consisting of specialists from Erasmus MC, CTRADA, INSERM (France) and Delphi (Germany). The workgroup will report to the INCANT Study Team.

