### Sample size

We carried out power calculations to determine the number of subjects needed to establish treatment effects on substance use measures within and across sites. To this end, we applied Monte Carlo simulation techniques with latent growth curve models [7]. A large number of samples were drawn, systematically varying effect size estimates, and a model was constructed for each sample. Each simulation tested a linear growth model for continuous outcomes with four time points (0, 6, 9 and 12 months), representing the four major INCANT assessment points. The result of interest was the regression coefficient between a dichotomous covariate representing treatment condition and the latent slope representing change in substance use over time.

In previous trials of MDFT [[4], for review] the size of the comparative treatment effect - the extent in which MDFT outperformed active control treatments - has generally been in the moderate to high range [8] of *d *= 0.6 or above. Conservatively assuming small effects, the models we generated predicted that power would be above 0.9 if the total cross-site sample consisted of 450 or more cases. For individual site analyses, assuming an effect size of 0.7, a sample of 100 per site would be needed to achieve power of 0.82.

We set the recruitment target at 480 cases. The sites in Germany, France and the Netherlands aim to recruit a maximum of 120 cases each. Because of budget limitations, Belgium and Switzerland settle for 60 cases each, with the intention to contribute to the cross-site statistical analyses.

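### The stated pooled model and power simulation name no therapist effect, although 54 therapists appear nested within arm; any positive therapist ICC would make the treatment comparison too precise

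*Protocol article*

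**What the plan says.** All references are to the protocol article.

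- **Analyses.** "We will pool the data from all subjects from all sites for analyses with country/site as a covariate". Repeated measures are to be analysed by a mixed model and by latent growth curve modelling (LGM). The variation that the section describes is between individuals' trajectories of change. No therapist or team term is named.
- **Experimental intervention (MDFT).** "MDFT is delivered by individual therapists who are part of teams of 3 - 5 CTRADA certified therapists".
- **Control condition.** TAU runs in the same centres and its sessions are individual, but it is "procedurally separated to avoid 'contamination' of therapists and participants between the experimental and control conditions".
- **Therapists.** "All MDFT (n = 25) and TAU therapists (n = 29) are experienced in treating adolescents with multiple problem behaviour". The two groups are listed and compared as separate sets.
- **Sample size.** The simulation tests the regression of the latent slope on a two-level treatment covariate; no therapist level is described. The result is that "power would be above 0.9 if the total cross-site sample consisted of 450 or more cases", "Conservatively assuming small effects", with no number attached to the effect. The section adds: "We set the recruitment target at 480 cases".

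**The concern.** Cases treated by the same therapist may have more similar outcomes than cases treated by different therapists. If each therapist serves one arm, randomizing cases does not balance therapists between arms. The difference between the average MDFT therapist and the average TAU therapist becomes part of the estimated treatment effect, and its sampling error has to be counted.

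A site covariate does not count it. Site removes only what both arms at a site share, whereas therapist variation arises within site and within arm. A model with site and individual growth but no therapist level therefore treats about 8 or 9 cases per therapist as independent.

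At stake is the error rate of the main MDFT-TAU comparison: a few strong or weak therapists could yield a significant result. The stated power would be too high for the same reason.

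**Working it through.** **Inputs from the article.** 25 MDFT and 29 TAU therapists, 54 in all; 450 cases for the stated power; a target of 480 (3 × 120 + 2 × 60).

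**Assumptions.** Therapist ICC of 0, 0.01, 0.02, 0.05 or 0.10; equal caseloads; 1:1 allocation; two-sided 5% test. The three-arm French site departs from 1:1 and is ignored here.

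**Step 1: the plan's own power.** It cannot be reproduced, because the effect size and the growth-model parameters are not given. A plain two-sample formula at 450 cases gives power 0.56 at d = 0.2, 0.89 at d = 0.3 and 0.91 at d = 0.31. This neither confirms nor refutes the stated figure, so the steps below start from 0.90 at 450.

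**Step 2: caseload.** At 450 cases: 225/25 = 9.0 per MDFT therapist and 225/29 = 7.8 per TAU therapist (450/54 = 8.3 overall). At 480 cases: 9.6 and 8.3 (480/54 = 8.9 overall).

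**Step 3: formulas.**
- Design effect (DE): the mean over the two arms of 1 + (m − 1) × ICC, where m is the caseload. Example at 450 cases and ICC 0.05: (1.400 + 1.338)/2 = 1.369.
- Real type I error of the unclustered test: 2 × [1 − Φ(1.96/√DE)]. Example: 1.96/√1.369 = 1.675, which gives 9.4%.
- Nominal interval width as a share of the correct width: 1/√DE.
- Effective N: N/DE.
- Power with clustering modelled: Φ(3.24 × √(effective N/450) − 1.96), where 3.24 = 1.28 + 1.96 corresponds to 0.90 at 450 independent cases.

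**Step 4: results at 450 cases.**

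| ICC | DE | Type I error | Interval width | Effective N | Power |
|---|---|---|---|---|---|
| 0 | 1.00 | 5.0% | 100% | 450 | 0.90 |
| 0.01 | 1.07 | 5.9% | 97% | 419 | 0.88 |
| 0.02 | 1.15 | 6.7% | 93% | 392 | 0.86 |
| 0.05 | 1.37 | 9.4% | 86% | 329 | 0.79 |
| 0.10 | 1.74 | 13.7% | 76% | 259 | 0.69 |

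**Step 5: results at 480 cases, still anchored at 0.90 for 450.**

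| ICC | DE | Type I error | Effective N | Power |
|---|---|---|---|---|
| 0 | 1.00 | 5.0% | 480 | 0.92 |
| 0.01 | 1.08 | 5.9% | 445 | 0.90 |
| 0.02 | 1.16 | 6.9% | 414 | 0.87 |
| 0.05 | 1.40 | 9.7% | 344 | 0.81 |
| 0.10 | 1.79 | 14.3% | 268 | 0.71 |

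**Step 6: does a site covariate help?** A simulation of 20,000 replicates used 480 cases, five sites, 25 + 29 therapists nested in arm (their split across sites assumed) and a linear model with site terms. Type I error was 4.9, 6.1, 7.1, 9.5 and 14.6% at ICC 0, 0.01, 0.02, 0.05 and 0.10. An analysis at therapist level on the same data, weighted using the simulated ICC, gave 4.9 to 5.2% throughout. Site adjustment leaves the inflation in place; accounting for therapist removes it.

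**Step 7: unequal caseloads.** With a coefficient of variation of 0.5 (assumed) at 450 cases, DE = 1 + [(1 + 0.25) × 8.33 − 1] × ICC. Type I error is then 6.1, 10.6 and 16.0% at ICC 0.01, 0.05 and 0.10.

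**The case against.** - **A condensed article may leave the random-effects structure to the full plan.** This stands in part. The Analyses section does not say that country/site is the only term, so a reader who infers that therapist effects are excluded goes beyond the text. But the section is not silent: it names the covariate, the models and the level at which change varies, and the Sample size section describes the simulated model. The point concerns what those passages state.
- **The ICC may be zero.** This stands. A reader might infer that the intervals are in fact too narrow and that type I error does exceed 5%. The documents do not support that, because they give no ICC.
- **One arm per therapist is inferred.** This stands. No sentence says so, though the separate therapist lists and the procedural separation point clearly to it.
- **Leaving out the stratification factors pulls the other way.** This is true at the low end. If gender, age and cannabis use explained 10% of the variance (assumed) and were not in the model, DE would be multiplied by about 0.9. Type I error at 450 cases would then be about 4.6% at ICC 0.01, but still about 7.7% at 0.05 and 11.7% at 0.10. One omission should not be relied on to cancel another.
- **The calculation is not the planned model.** This stands. It uses a single outcome, whereas the powered quantity is treatment on the latent slope. The ICC that matters is that of the slope, so the figures indicate size and are not predictions.
- **The power loss is easily overstated.** This stands if the loss is applied to exactly 0.90 at 480 cases. The plan states power above 0.9 at 450, so the 30 extra cases recover part of the loss, as Step 5 shows.
- **Therapist codes could reveal the arm.** This is a fair practical point. The Blinding section keeps central staff unaware of condition, and 25 against 29 codes could give it away.

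**Conclusion.** The point holds in conditional form. The stated pooled model and the power simulation name no therapist effect, 54 therapists appear to be nested within arm, and a country/site covariate cannot absorb their variation. At ICC 0 nothing is lost. Across an assumed range of 0.01 to 0.10, type I error of the unclustered test would be about 6% to 14%. Power of 0.90 at 450 cases would become about 0.88 to 0.69, or about 0.90 to 0.71 with the target of 480. At ICC 0.01 the effect is small; at 0.05 or more it is material for the primary comparison. These figures rest on the assumed ICC, equal caseloads, 1:1 allocation, a two-sided 5% test and a single-outcome approximation to the slope model.

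**What to change.** 1. In the mixed model and the LGM, add therapist (nested in site and arm) as a random effect, on the slope as well as the level where the treatment effect is read from the slope. Alternatively, use therapist-clustered standard errors. Either way, apply a small-sample degrees-of-freedom correction.
2. Assign cases that never start treatment to the therapist scheduled at randomization, so that all randomized cases stay in the analysis.
3. Use coded therapist identifiers, chosen so that central analysts stay unaware of condition as far as possible.
4. Restate the power as conditional on an assumed therapist ICC, with a range.

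**Cost.** Confidence intervals become somewhat wider and the power figure less favourable. Therapist codes must be linked to the central database. The section on monitoring of treatment integrity already requires contact logs or treatment-register data from therapists in all conditions, but the article does not say that therapist identity is held centrally, so the link may have to be built. Recruitment, treatment and assessments are unchanged.

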## Discussion

There are differences in mainstream treatment philosophy between the countries taking part in INCANT. Thanks to a pilot study and intensive international consultation and training, these differences eventually appeared to be surmountable or at least not strong enough to block the trial here reported. INCANT is firmly underway, with steady enrolment of cases.

INCANT is more than a treatment trial. In a way, it is also a social and cultural experiment. At first, European officials thought that MDFT, as it originates from the USA, might be at odds with European practices and traditions. However, while preparing for INCANT the differences between European countries appeared to be bigger than the difference between any of them and Miami. Nevertheless, MDFT proved to be adaptable to European treatment settings in all of the five countries, such that procedures are mutually comparable (except for referral source).

In some of our five countries, there was hardly any experience, if at all, with conducting an RCT in youth (addiction, mental, forensic) care. Making referral authorities, treatment and funding agencies accept the principle of randomization was seen as (almost) a bridge too far. If INCANT yields any comparative treatment effects remains to be seen, but INCANT did succeed in making a trial happen in rather uncharted territory.

